### **6.2.3 Microbiologic Cure of TB**

Microbiologic cure of TB is defined as negative mycobacterial cultures on 2 or more consecutive occasions including one culture done after 5 months of therapy**.**

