## 4.4 Exclusion Criteria for Randomization

Randomization into the study intervention will occur between weeks 2 and 4 following study entry and initiation of standard anti-TB therapy. The study population will be restricted to patients exhibiting none of the following contraindications to starting the punctuated antiretroviral intervention during this assessment period:

1. Fever > 38.0˚ C;
2. WHO stage IV AIDS-defining condition;
3. Weight < 40 Kg;
4. CD4+ count < 350 cells/ml at screening
5. AST > 2.0 times upper limit of normal;
6. Creatinine > 2 mg/dL;
7. Hemoglobin < 9.5 g/dL;
8. Absolute neutrophil count < 1000 cells;
9. Positive serum or urine pregnancy test for women of childbearing potential;
10. Current treatment with Ribavirin or Doxorubicin;

Laboratory values must be within the acceptable range within 14 days prior to randomization to Step 2.

Post randomization exclusion:

Final determination of eligibility will be made after review of drug susceptibility testing results on an initial sputum isolate and results of all sputum cultures. Subjects found to have multi-drug resistant strains will be excluded from randomization.  These subjects will be withdrawn from the study but treatment and follow-up will be provided for MDR TB.

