## 6.2 Response to Antituberculosis Therapy

### **6.2.1 Sputum Culture Conversion**

The proportion of patients with MTB sputum conversion (from positive to negative) per treatment group will be determined at months 1 and 2. For an individual patient, sputum culture conversion will be defined as the absence of mycobacterial growth on solid media without a subsequent positive sputum culture during the first 16 weeks of therapy. Subjects with all sputum cultures negative at 2 consecutive time points who are clinically stable or improving and unable to produce sputum will be considered to have converted their sputum at the date of the first of the two specimens. Patients with one negative sputum culture after a period of treatment, who are clinically stable or improving and unable to produce sputum thereafter, will be considered to have converted their sputum culture at the time of the first specimen.

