### **7.3.2 Intervention Phase Study Visit**

Following treatment assignment and initiation of study intervention, patients will be evaluated one and two weeks after initiation of ARV treatment and then monthly during study intervention phase (see Appendix I, Step 2).

1. Medical history and physical examination including weight, major TB and HIV-related signs and symptoms and primary study outcomes (Week, 2, Months 1, 2, 3, 4, 5, 6, and as indicated)
2. New diagnoses and/or hospitalizations since the last study visit (Week 2, Months 1, 2, 3, 4, 5, 6, and as indicated)
3. Posterior-anterior chest X-ray (8 weeks, and between 22 and 24 weeks)
4. Adverse experiences survey (Week 2, months 1, 2, 3, 4, 5, 6, and as indicated)
5. Sputum semi-quantitative AFB smear and culture on solid media X 2 (between 4 & 6 weeks, 8 weeks, and between weeks 18 & 20 from the start of anti-TB treatment)
6. MTB drug susceptibility (as clinically indicated)
7. Urine or serum -HCG pregnancy test (females of child bearing potential only) (Week 2, Months 1, 2, 3, 4, 5, 6, and as indicated)
8. CBC, differential white blood cell and platelet count (Week 2, Months 1, 2, 3, 6, and as indicated)
9. Serum aspartate aminotransferase (AST), serum total bilirubin (Week 2, Months 1, 2, 3, 6, and as indicated)
10. Serum creatinine (as clinically indicated)
11. CD4+ lymphocyte counts (Weeks 2, Months 1, 3, 6, and as clinically indicated)
12. Plasma HIV RNA by Roche Amplicor (Weeks 2, Months 3 and 6, and as clinically indicated)
13. Adherence Questionnaire for antituberculosis and antiretroviral therapy (Week 2, Months 1, 2, 3, 4, 5, 6, and as indicated)
14. Quality of life assessment (month 6)
15. Urine INH testing (Week 2, Months 1, 2, 3, 4, 5, 6)
16. Plasma storage (Weeks 1, 2, Months 1, 2, 3 and 6)
17. PBMC storage/ immune function (Week 2, Months 3, and 6)
18. Store MTB isolate for DNA fingerprinting (All isolates from positive cultures of suspected relapse cases will be stored at -70° C for DNA finger printing with the patient’s initial isolate, as clinically indicated)
19. Disease specific diagnostic test (as clinically indicated)

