### **7.3.3 Post-Study Intervention Follow-up (prior to study outcome)**

Each subject will undergo the following examinations during follow‑up after completion of the six-month ARV Intervention Phase (see Appendix I, Step 2). After completing the intervention phase, patients will be seen monthly until month 12, and then patients will be evaluated every 3 months for a minimum of two years. A patient may be followed up to a maximum of five years depending on the date of enrollment; patients will be evaluated every 4 months after the first three years.

1. Medical history and physical examination including weight, major TB and HIV-related signs and symptoms and primary study outcomes (Months 7, 8, 9, 10, 11, 12, 15, 18, 21, 24, 27, 30, 33, 36 and *every 4 months thereafter or as clinically indicated*)
2. New diagnoses and/or hospitalizations since the last study visit (Months 7, 8, 9, 10, 11, 12, 15, 18, 21, 24, 27, 30, 33, 36 and *every 4 months thereafter or as clinically indicated*)
3. Posterior-anterior chest X-ray (Months 12, 18, and as clinically indicated)
4. Adverse experiences survey (Months 7, 8, 9, 10, 11, 12, 15, 18, 21, 24, 27, 30, 33, 36 and *every 4 months thereafter or as clinically indicated*)
5. Sputum semi-quantitative AFB smear and culture on solid media X 2 (Months 12 and 18, *or as clinically indicated*)
6. MTB drug susceptibility (as clinically indicated)
7. Urine or serum -HCG pregnancy test (as clinically indicated)
8. CBC differential white blood cell and platelet count (Months 9, 12, 15, 18, 21, 24, 27, 30, 33, 36 and *every 4 months thereafter or as clinically indicated)*
9. Serum aspartate aminotransferase (AST), serum total bilirubin (as clinically indicated)
10. Serum Creatinine (as clinically indicated)
11. CD4+ lymphocyte counts (Months 9, 12, 15, 18, 21, 24, 27, 30, 33, 36 and *every 4 months thereafter or as clinically indicated*)
12. Plasma HIV RNA by Roche Amplicor (Months 9, 12, 18, 24, 30, 36, and then annually or as clinically indicated)
13. Quality of life assessment (months 12, 18, 24, 30 and 36)
14. Plasma storage (Months 9, 12, 18, 24, 30, 36 and *every 4 months thereafter, or as clinically indicated*)
15. PBMC storage/ immune function (Months 9 and 12, *or as clinically indicated*)
16. Store MTB isolate for DNA fingerprinting (All isolates from positive cultures of suspected relapse cases will be stored at -70° C for DNA finger printing with the patient’s initial isolate, as clinically indicated)

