### **7.4.2 Post- Primary Outcome - Antiretroviral Therapy Follow-up Visits**

Prior to being started on self-administered ARV therapy and entry to STEP 3, a pre-ARV baseline evaluation will be completed; this will include the following examination (appendix I, Step 3):

1. HIV RNA Roche Amplicor
2. Quality of life assessment
3. Plasma storage
4. PBMC storage/ immune function (Flow cytometry to assess cell surface activation markers, EliSpot to assess CD4 and CD8 T cell specificity to HIV and microbial peptides, Whole blood assays to determine antigen specific response to HIV and microbial antigens)

Assessments from confirmation of study outcome, or ARV safety evaluation may be used for pre-antiretroviral baseline if they were completed within two weeks before ARV baseline.

Patients will then be started on self-administered, ARV therapy and enter STEP 3 (Section 5.0 describing the initiation of therapy). Patients will receive detailed counseling about treatment with antiretroviral therapy. They will be informed that adherence measures will be made including unannounced home visits to record self-reported adherence and pill counts. Below is the schedule for STEP 3:

1. Medical history and physical examination including weight (Week 2, months 1, 2, 3, 6, 9, 12, 15, 18, 21, 24, 27, 30, 33, 36, and then every 4 months or as clinically indicated)
2. Adverse experiences survey (Week 2, months 1, 2, 3, 6, 9, 12, 15, 18, 21, 24, 27, 30, 33, 36, and then every 4 months or as clinically indicated)
3. New diagnoses and/or hospitalizations since the last study visit (Week 2, months 1, 2, 3, 6, 9, 12, 15, 18, 21, 24, 27, 30, 33, 36, and then every 4 months or as clinically indicated)
4. Urine or serum -HCG pregnancy test (if suspect)
5. CD4+ lymphocyte count (months 3, 6, 12, 18, 24, 30, 36, then every 4 months thereafter or as clinically indicated)
6. CBC with differential and platelet count (months 3, 6, 12, 18, 24, 30, 36, then every 4 months thereafter or as clinically indicated)
7. Posterior-anterior chest X-ray (as clinically indicated)
8. Sputum semi-quantitative AFB smear and culture on solid media X 2 (as clinically indicated)
9. MTB drug susceptibility (as clinically indicated)
10. Serum aspartate aminotransferase (AST), serum bilirubin (months 1, 2, 6, 12, 18, 24, 30, 36, and every 4 months thereafter or as clinically indicated)
11. Serum creatinine (as clinically indicated)

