#### **10.2.2.2 Specific Aim 2**

To determine whether a punctuated six-month course of ARV therapy during treatment of active TB will improve the response to antituberculous therapy, as measured by one month culture conversion, treatment failure, and relapse TB, among patients with active TB and CD4+ cell count above 350 cells/µL.

The analysis of this Specific Aim will include only patients with active TB that have been randomized in the clinical trial. The effect of ARV treatment on the response to antituberculous therapy will be evaluated by comparing the proportion of subjects with negative smears or cultures at one and two months (chi square test). A similar analysis will be performed for antituberculosis treatment failure in the ARV treatment arms compared to the reference arm.

Previous published studies of TB in HIV infection estimate relapse rates between 3 and 10%; we thus expect to identify between 10 to 35 relapse cases of TB during the study. The cumulative incidence of TB relapse will be estimated by group using Kaplan-Meier methods; incidence density methods will also be used to measure the number of relapses per 100 person-years of observation after completing antituberculous treatment according to ARV treatment group. The incidence density ratio (95% confidence interval) will be estimated to compare incidence in treated and reference groups. Cox regression analysis will be used to determine whether punctuated ARV therapy is associated with relapse after adjusting for covariates. The analysis will account for the different treatment histories by using time-dependent Cox proportional hazards analysis. The analysis will be further stratified according to relapses due to reactivation and reinfection based on the RFLP patterns.

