**APPENDIX I. Study Schedule, STEP 2**

Delaying HIV disease Progression with Punctuated Antiretroviral Therapy in Patients with Tuberculosis

Study Intervention, Follow-up and Laboratory Testing Schedule

|  | **STEP 2** | | | | | | | | | | | | | | | | | | | | | | | | |
| --- | --- | --- | --- | --- | --- | --- | --- | --- | --- | --- | --- | --- | --- | --- | --- | --- | --- | --- | --- | --- | --- | --- | --- | --- | --- |
|  |  | **Study Intervention Phase**  **(Months)** | | | | | | | | **Post-Study Intervention Follow-up (prior to study endpoint)**  **(Months)** | | | | | | | | | | | | | | | |
| Base  Line (Wk0) | Wk 1 | **Wk 2** | 1 | **2** | **3** | **4** | **5** | **6** | **7** | **8** | **9** | **10** | **11** | **12** | **15** | **18** | **21** | **24** | **27** | **30** | **33** | **36** | Extended Follow-upa | SV |
| **H&P, weight** |  |  | X | X | X | X | X | X | X | X | X | X | X | X | X | X | X | X | X | X | X | X | X | X | X |
| **New diagnoses/ hospitalizations survey** |  |  | X | X | X | X | X | X | X | X | X | X | X | X | X | X | X | X | X | X | X | X | X | X | X |
| **PA chest X-ray b,c** |  | week 8, and between weeks 22 & 24 from start of anti-TB Rx | | | | | | | |  |  |  |  |  | X |  | X |  |  |  |  |  |  |  | Xl |
| **AE Survey** |  |  | X | X | X | X | X | X | X | X | X | X | X | X | X | X | X | X | X | X | X | X | X | X | X |
| **Sputum AFB smear & culture on solid media c** |  |  | between wks 4-6, week 8, and between weeks 18-20 from start of anti-TB Rx (x2) | | | | | | |  |  |  |  |  | XX |  | XX |  |  |  |  |  |  |  | Xl |
| **MTB drug susceptibility** |  |  | As clinically indicated | | | | | | | | | | | | | | | | | | | | | | |
| **Pregnancy test (females) d** |  |  | X | X | X | X | X | X | X | As clinically indicated | | | | | | | | | | | | | | | |
| **CBC w/ differential & platelet count e** |  |  | X | X | X | X |  |  | X |  |  | X |  |  | X | X | X | X | X | X | X | X | X | X | Xl |
| **AST, serum total bilirubin f, g** |  |  | X | X | X | X |  |  | X | As clinically indicated | | | | | | | | | | | | | | | |
| **Serum creatinine h** |  |  | As clinically indicated | | | | | | | | | | | | | | | | | | | | | | |
| **CD4+ lymphocyte count i** |  |  | X | X |  | X |  |  | X |  |  | X |  |  | X | X | X | X | X | X | X | X | X | X | Xl |
| **HIV RNA Roche Amplicor** | X |  | X |  |  | X |  |  | X |  |  | X |  |  | X |  | X |  | X |  | X |  | X | Xm | Xl |

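### The microbiologic cure definition needs a culture after 5 months of therapy, but the last scheduled on-treatment sputum is at weeks 18-20, and the 16-week conversion check has no scheduled culture to test a month-2 conversion

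*Protocol*

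**What the plan says.** The protocol synopsis lists microbiologic cure of TB among the secondary endpoints, and Table 6 lists cure of active TB under Aim 2. Section 6.2.3 defines microbiologic cure as "negative mycobacterial cultures on 2 or more consecutive occasions including one culture done after 5 months of therapy".

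Section 7.3.2 schedules sputum during treatment "between 4 & 6 weeks, 8 weeks, and between weeks 18 & 20 from the start of anti-TB treatment". Appendix I, Step 2, gives the same three windows: "between wks 4-6, week 8, and between weeks 18-20 from start of anti-TB Rx (x2". After the intervention phase, Section 7.3.3 has "Sputum semi-quantitative AFB smear and culture on solid media X 2 (Months 12 and 18", and otherwise only on clinical indication. Once a patient has entered Step 3, Section 7.4.2 has "Sputum semi-quantitative AFB smear and culture on solid media X 2 (as clinically indicated". Section 5.1.1.1 sets the TB course at six months.

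Section 6.2.1 determines culture conversion at months 1 and 2 and requires a culture without growth, "without a subsequent positive sputum culture during the first 16 weeks of therapy".

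**The concern.** An endpoint definition and the visit schedule have to describe the same cultures. Here the definition asks for a negative culture later than any the schedule collects during treatment, and the next scheduled one comes long after treatment has stopped. Cure then rests either on cultures taken because someone was ill or on a late post-treatment culture, where a positive result may be a relapse under Section 6.2.6 and not a failure to cure. Patients already in Step 3 have no such culture scheduled, so missing cure data would be tied to HIV progression, which is the outcome the intervention is meant to change. An analysis plan can choose how to handle such gaps, but it cannot supply a culture that was not collected.

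Conversion has a related problem. The look-ahead is meant to remove transient negatives, but for month 2 it covers a period with no scheduled culture.

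**Working it through.** **Inputs.** Sputum windows in weeks from the start of anti-TB treatment: 4-6, 8 and 18-20 (7.3.2, Appendix I Step 2). Post-intervention cultures: months 12 and 18 (7.3.3). TB course: 6 months (5.1.1.1). Randomization: weeks 2 to 4 of TB therapy (4.4). Cure: a culture after 5 months (6.2.3). Conversion look-ahead: 16 weeks (6.2.1). Treatment failure: 4 or more months of effective treatment (6.2.5). One calendar month = 365.25 / 12 / 7 = 4.348 weeks.

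**Step 1: does the last on-treatment culture reach five months?**
- Five months = 5 × 4.348 = week 21.7.
- Week 18 = 18 / 4.348 = 4.14 months; week 20 = 20 / 4.348 = 4.60 months.
- Shortfall: 21.7 − 20 = 1.7 weeks to 21.7 − 18 = 3.7 weeks.
- With 28-day months the window is 18/4 = 4.5 to 20/4 = 5.0 months. Its last day reaches the boundary but does not pass it.
- Treatment ends at 6 × 4.348 = week 26.1. No culture is scheduled between week 20 and that point.

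**Step 2: when is the next scheduled culture?** Assume Step 2 months count from randomization, since Appendix I labels the Step 2 baseline as week 0.
- Randomized at week 2: 2 + 12 × 4.348 = TB week 54.2, or (54.2 − 26.1) / 4.348 ≈ 6.5 months after treatment ends.
- Randomized at week 4: 4 + 12 × 4.348 = TB week 56.2, or (56.2 − 26.1) / 4.348 ≈ 6.9 months after treatment ends.

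**Step 3: how many patients might have left Step 2 by then?** This is an illustration using the sample-size assumptions in Section 10.1: constant hazard, and 50% progression in the reference group at 2 or 3 years. The effect-size formula is not legible in the text, so I assume that 35% means a hazard ratio of 0.65.
- 50% at 2 years: reference 1 − 0.5^(1/2) = 29%; punctuated 1 − 0.5^(0.65/2) = 20%.
- 50% at 3 years: reference 1 − 0.5^(1/3) = 21%; punctuated 1 − 0.5^(0.65/3) = 14%.

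These are proportions with a primary outcome by month 12. Some of these patients would wait in Step 2 until fit for ARV, so the figures only approximate those without a scheduled culture. If the intervention works as planned, the missing share differs between arms by about 7 to 9 percentage points.

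**Step 4: can the 16-week look-ahead be tested?**
- Month-1 conversion (weeks 4-6): the week-8 culture lies inside the 16 weeks and can overturn it.
- Month-2 conversion (week 8): the next scheduled culture is at weeks 18-20, which is 2 to 4 weeks after the look-ahead closes. No scheduled culture can overturn it.
- A patient negative at week 8 and positive with at least 5 colonies at weeks 18-20 can count both as a month-2 converter (6.2.1) and as a treatment failure (6.2.5).

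**Step 5: does treatment failure fit?** Four months = 4 × 4.348 = week 17.4, and weeks 18-20 lie beyond it. It fits.

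**The case against.** The strongest reply is that Section 6.2.3 does not say the late culture must be taken on treatment. A negative culture at weeks 18-20 followed by a negative at month 12 meets the definition literally. That stands. A reader might infer that cure is undefined for every patient, or that nobody can be classified as cured; the documents do not support this. What remains is that the qualifying culture comes more than six months after treatment and is not scheduled in Step 3.

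Three other stronger readings are tempting and also fail:
- **That the conversion check can never fail.** It can for month 1, through the week-8 culture, and sick-visit cultures (7.5) can trigger it at either time. Only month 2 lacks a scheduled test.
- **That some month-1 samples are taken before any ARV exposure.** Section 4.4 says "Randomization into the study intervention will occur between weeks 2 and 4 following study entry and initiation of standard anti-TB therapy", so the two windows share week 4 and arithmetic alone gives 0 to 4 weeks of exposure. But Section 7.3.1 lists no sputum at randomization, and the Appendix I sputum entry begins at Step 2 week 2. That is TB week 4, 5 or 6 for randomization at week 2, 3 or 4, which implies about two weeks of ARV. No minimum is written, so zero is not excluded, but it is not shown to occur.
- **That Aim 2 rests on month 1 alone.** The aim statement in 10.2.2.2 does read "as measured by one month culture conversion, treatment failure, and relapse TB", but the analysis paragraph beneath it compares both one and two months. There is no ground for demoting month 1.

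It is also fair to say that the impact is limited. Cure is one of several secondary endpoints, clinical cure (6.2.4) carries no five-month condition, and the primary outcome is untouched.

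**Conclusion.** The point holds in a limited form. The cure definition and the sputum schedule disagree by 1.7 to 3.7 weeks in calendar months. In 28-day months the window at best touches the boundary. As written, cure can be met only through unscheduled cultures or through the Step 2 month-12 culture at about TB week 54-56. That culture mixes cure with relapse, and its availability depends on the primary outcome. Separately, a month-2 conversion cannot be contradicted by scheduled data within the 16-week look-ahead, so month-1 and month-2 conversion are not held to the same standard.

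The timing result rests on the protocol's own windows, which the text and Appendix I state identically. The month-12 position assumes that Step 2 months run from randomization. The difference in missing cultures between arms is an illustration that borrows the sample-size assumptions. A reader might extend the finding to all the TB-response endpoints; treatment failure fits the schedule, and no misfit is shown for relapse. The matter is worth correcting but does not threaten the primary analysis.

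**What to change.** Reconcile Section 6.2.3 with Section 7.3.2 and Appendix I Step 2 so that a scheduled on-treatment culture can satisfy the cure definition. The simplest way is to restate the definition to match the weeks 18-20 culture. This is a text change with no new visit or sample.

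If the sputum window is moved later instead, the cost has to be weighed. Weeks 18-20 is the only scheduled on-treatment culture that can detect treatment failure under 6.2.5. Moving it to, say, the existing weeks 22-24 chest X-ray window would leave no scheduled culture between week 8 and week 22.

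Extend the conversion look-ahead in Section 6.2.1 from 16 weeks to the last scheduled on-treatment culture at weeks 18-20. This also uses samples already planned. Its only cost is that conversion status becomes final a few weeks later.

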### **6.2.4 Clinical Cure of TB**

Clinical cure of TB is defined as a patient who (1) has completed anti-TB therapy (6.2.2); (2) has a negative smear or culture when last tested; (3) no new lesions on chest x-ray; and (4) no clinical signs or symptoms of active TB.

### **6.2.5 Treatment Failure**

A culture-positive treatment failure is defined as a patient who is receiving anti-TB treatment and has at least one sputum mycobacterial culture growing at least 5 colonies of *M. tuberculosis* (MTB) on solid medium after completing 4 or more months of effective anti-TB treatment. Patients who default before completing anti-TB treatment and return later with culture-positive tuberculosis will be termed failures after non-adherence.

Patients will be retreated in accordance with applicable national TB program guidelines and drug susceptibility testing results.

### **6.2.6 Relapse of Tuberculosis**

A relapse case of tuberculosis is defined as incident tuberculosis that develops in a patient who completed a course of antituberculosis treatment AND had clinical and/or microbiologic evidence for response to treatment in the earlier episode. Relapse cases may be defined as either clinical or culture-confirmed relapses.

- A clinical relapse is defined as a patient with clinical and/or radiographic evidence of recurrent tuberculosis not confirmed by a positive mycobacterial culture during follow-up after successful completion of initial anti-TB treatment (defined in 6.2.2).

- A culture-confirmed relapse is defined as a patient with clinical and/or radiographic evidence of recurrent tuberculosis that is confirmed with one or more positive cultures for mycobacterial growth. A mycobacterial culture is considered positive as follows: 1) a mycobacterial culture has at least 5 colonies of *M. tuberculosis* (MTB) on solid medium; 2) a mycobacterial culture

growing fewer that 5 colonies of MTB on solid medium with the same RFLP pattern as strain causing initial disease; or 3) mycobacterial growth detect using BACTEC.

Clinical evidence of active tuberculosis includes clinical signs (cough, consolidation, lymphadenopathy, wasting, fever, meningitis, ascites, etc.) and symptoms (cough, fever, weight loss, anorexia, headache, abdominal distention, etc.). Radiographic evidence includes an abnormal chest X-ray with findings consistent with TB.

In some unusual instances, positive mycobacterial cultures are found in patients without signs or symptoms of active TB in whom routine screening is performed. In these cases, patients with isolated single positive sputum cultures will not be considered to be relapses unless, as described above, they have signs or symptoms consistent with active tuberculosis and respond to antituberculosis treatment. For patients without signs or symptoms who have multiple positive cultures, these patients will be considered probable cases.

All recurrent cases of tuberculosis will be reviewed by the Clinical Review Committee who will be blinded to the study arm. This panel will classify all recurrent cases according to a standard set of criteria. Using this classification system, recurrent cases are classified as definite (culture-confirmed), probable (signs, symptoms, and laboratory findings consistent with active tuberculosis without a positive culture AND response to antituberculosis therapy), possible (signs or symptoms of active tuberculosis without confirmatory laboratory findings AND response to antituberculosis therapy), and unlikely (none of the above categories). Where reviewers differ in the classification of cases, a consensus decision is made after all reviewers meet to discuss the case. For the purposes of this study, only definite and probable cases will be categorized as relapses.

Restriction fragment length polymorphism (RFLP) analysis will be used to determine whether the relapse is the result of reactivation of previous disease (matched RFLP patterns) or of reinfection (non-matched RFLP patterns).

